### Strengths and Limitations

Currently, the GBD is unable to include lifestyle exposures such as dietary intake as a risk for CMDs due to the following: difficulties determining directionality and causality, inconsistency in dietary variables and methods, small sample sizes, and lack of global representation. A strength of the GLAD project is that it will address all these methodological considerations. We will (1) prioritize prospective studies using incident cases (ie, excluding those with baseline CMDs) to obtain risks of CMDs attributable to dietary intake, and not the other way around (to determine directionality or temporality), (2) include all study designs (including from experimental or randomized controlled trials to strengthen causal conclusions), (3) conduct harmonized data analyses approved by the GBD (to improve consistency between studies and specificity of the diet-CMD relationship), and (4) pool data from multiple studies from around the world (to address sample size and global representation).

Despite the clear strengths of the GLAD project, there are some limitations. First, the GBD study is an ongoing and dynamic study, and definitions and methods are constantly evolving. Every effort will be made to ensure the taskforce are following GBD-approved methods, however, some changes from the GBD may be unavoidable. Second, since the GBD does not currently include ultraprocessed food as a dietary risk factor, the definitions and methods used by the task force may not reflect those used in future iterations of the GBD. Finally, although food intakes provide a general overview of diet quality, people do not eat food items in isolation. The current methods used by the GBD do not currently consider dietary patterns. This may limit interpretations to specific food items and not to an overall dietary pattern.

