^c^Outcomes must be binary (condition present vs condition absent). For studies that only use symptom scales, validated cutoffs can be used to determine condition present versus condition absent (refer to Multimedia Appendix 1).

^d^*DSM-IV-TR*: *Diagnostic and Statistical Manual of Mental Disorders (Fourth Edition, Text Revision)*.

^e^*ICD-10*: *International Statistical Classification of Diseases, Tenth Revision*.

^f^MDD: major depressive disorder.

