#### Covariates and Confounders

To address the anticipated heterogeneity of member studies’ available data, a set of core confounders are provided for the purpose of generating a consistent minimally adjusted analysis. The conduct of additional analyses (eg, using additional variables, fitting sensitivity models, or exploratory analyses) is at the discretion of the study author or authors based on available data and reviewer requests when studies are submitted for publication.

To be included in the GLAD project, member studies must adhere to the iteratively adjusted models (Textbox 1).

The iteratively adjusted statistical models required for the Global burden of disease Lifestyle And mental Disorders (GLAD) task force.Model 1: Unadjusted model, with the dietary variable (as listed in Table 2) as the exposure and depression or anxiety as the outcome.Model 2: Minimally adjusted model, with the dietary variable of interest, depression or anxiety, and with baseline mental disorder status (or lifetime history of mental disorders for cross-sectional studies), age, sex, and a measure of socioeconomic status, such as household income, employment status, or education.Sensitivity model: Same as model 2, but with adjustment for total energy intake.

Of particular relevance in nutritional epidemiology are methods for adjusting for energy intake. Intake of specific nutrients are correlated with total energy intake, and so appropriate adjustment is required to disentangle the effect of the nutrient from the effect of energy. For example, an individual may alter intake of a specific nutrient by changing dietary composition, and not by changing total energy intake. As such, controlling energy intake can reduce confounding, and failure to appropriately control for total energy intake may nullify associations between nutrient intake and disease outcomes [27]. Given the correlation between nutrient intake and energy, the application of Willett’s residual method is recommended to account for total energy intake [27]. This involves fitting a regression model with the dietary variable as the outcome and total energy intake as the exposure, predicting residuals from this model, and then using these predicted residuals in the analysis models [27].

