#### Estimating Risk Ratios, Odds Ratios, and Hazards Ratios

Each study is required to use risk ratios (estimated by Poisson regression with robust SE) as the primary means of assessing the association of dietary intake with CMDs. Risk ratios are based on incident cases, and so models will need to exclude participants with depression or anxiety at baseline. Furthermore, to determine incident risk, studies must have dietary exposures at baseline and depression, or anxiety measured at a subsequent time point. Where the estimation of a risk ratio is not possible (refer to Figure 2), for example, where the total number of people exposed at baseline is not available (such as for retrospective or case-control studies) [29], odds ratios are estimated using standard logistic regression techniques. Where only time-to-event data are available, hazard ratios are used, estimated by a Cox proportional hazards model. For rigor, all effect estimates will be accompanied by a 95% CI and exact *P* value [30].

Models can be fitted using any statistical analysis software, including R (R Core Team), SAS/STAT (SAS Institute Inc), Stata (StataCorp LLC), and SPSS (IBM Corp). Before fitting the relevant models, Member studies must assess model assumptions. Should any model assumptions be violated, an alternate approach to analysis may be selected. For example, the nonlinearity of continuous variables should be investigated, and transformations or nonlinear models fitted where necessary. Similarly, should any of the assumptions of Cox proportional hazards models be violated, alternative strategies will be deployed to account for these violations.

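### Excluding baseline cases fixes the order of measurement, not the direction of effect: subthreshold illness that already alters diet can remain in the risk ratios, and no required model checks for it

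*Protocol article*

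**What the plan says.** Strengths and Limitations lists the difficulty of establishing direction and causation among the reasons the GBD has no diet pairings for common mental disorders (CMDs). It then states: "A strength of the GLAD project is that it will address all these methodological considerations". For direction, the means is to give priority to prospective studies with incident cases, "excluding those with baseline CMDs) to obtain risks of CMDs attributable to dietary intake, and not the other way around".

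The working rules are elsewhere in the article:

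- **Exclusion** (Estimating Risk Ratios, Odds Ratios, and Hazards Ratios): "Risk ratios are based on incident cases, and so models will need to exclude participants with depression or anxiety at baseline".
- **Timing** (same section): "studies must have dietary exposures at baseline and depression, or anxiety measured at a subsequent time point". No minimum interval is given.
- **Case definition** (Table 2, footnote c): "Outcomes must be binary (condition present vs condition absent"; for studies that hold only symptom scales, "validated cutoffs can be used to determine condition present versus condition absent".
- **Required adjustment** (Covariates and Confounders, Textbox 1): Model 2 is fitted "with baseline mental disorder status (or lifetime history of mental disorders for cross-sectional studies), age, sex, and a measure of socioeconomic status". The one sensitivity model in Textbox 1 adds total energy intake. Further models are left to each study's authors.
- **Subgroups** (Estimating Risk Ratios, Odds Ratios, and Hazards Ratios): separate fits by year for cohorts with several follow-up waves, where data allow.

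**The concern.** Dropping baseline cases and measuring the outcome later shows that diet was recorded before the disorder was detected. It does not show that diet preceded the illness process.

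In a scale-based cohort, someone just below the cutoff at baseline counts as unaffected and stays in the risk set. That person may already eat differently because of emerging symptoms, and is also more likely than others to cross the cutoff at the next assessment. Diet and outcome are then associated through the symptoms, whether or not diet has any effect. The shorter the interval, the stronger this link is likely to be, and the rules accept any interval.

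The stakes come from the intended use. The Discussion (Anticipated Impact) expects the results to meet the GBD's evidence threshold for a causal relation. Direction is one of the obstacles the article names, and its limitations paragraph does not mention reverse causation. Pooling reduces random error but does not remove a bias that several cohorts share.

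**Working it through.** The documents give no figure on this point, so there is nothing to reproduce. The check has two parts.

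**1. The rules set side by side**

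- The exclusion removes only people who meet the binary definition at baseline. That subthreshold participants stay in follows from the exclusion rule and the cutoff together; no sentence says so directly.
- Once baseline cases of a disorder are excluded, baseline status for that disorder is the same for everyone left. The Model 2 covariate then adjusts for nothing on that disorder, and symptom severity is not among the covariates.
- The required sensitivity model concerns energy intake and does not bear on direction.
- The subgroup by year, on its natural reading, gives wave-specific estimates, so early and late follow-up could be compared. It applies only with several waves and is not specified as a check on reverse causation.

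**2. Can these rules give a non-null risk ratio when diet has no effect?**

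*Hand calculation.* All inputs are assumed. Let a share s of an intake group be subthreshold, with R times the onset risk p of the others. Group risk is p × [1 + s(R − 1)], so low versus high intake gives

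RR = [1 + s₁(R − 1)] / [1 + s₀(R − 1)].

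- s₁ = 0.20, s₀ = 0.12, R = 3: 1.40 / 1.24 = 1.129
- s₁ = 0.20, s₀ = 0.12, R = 4: 1.60 / 1.36 = 1.176
- s₁ = 0.15, s₀ = 0.12, R = 4: 1.45 / 1.36 = 1.066

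This is a crude two-group comparison, whereas Table 1, footnote c requires continuous exposures.

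*Simulation with the article's estimator.* This used Poisson regression with robust SE, baseline cases excluded, continuous diet, and 400,000 participants per scenario before exclusion. Assumed: standard-normal symptom scores at baseline and follow-up; a case is a score above the cutoff giving 10% or 15% prevalence; diet is correlated with baseline symptoms as shown (illness alters diet); diet has no effect on the outcome. A lower correlation between baseline and follow-up symptoms stands for a longer interval. RR per SD of diet:

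| Diet-symptom correlation | 10% prevalence; symptom correlation 0.7 / 0.5 / 0.3 | 15% prevalence; symptom correlation 0.7 / 0.5 / 0.3 |
|---|---|---|
| 0 | 1.010 / 1.002 / 1.005 | 0.999 / 1.000 / 0.999 |
| -0.1 | 0.924 / 0.945 / 0.966 | 0.932 / 0.955 / 0.969 |
| -0.2 | 0.841 / 0.885 / 0.937 | 0.867 / 0.907 / 0.942 |
| -0.3 | 0.776 / 0.831 / 0.885 | 0.798 / 0.854 / 0.919 |

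Three results follow.

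- With no diet-symptom correlation there is no bias; with one, the exclusion does not remove it.
- A longer interval shrinks the false association without abolishing it. At -0.2 and 10% prevalence, RR moves from 0.84 to 0.94.
- Adding the continuous baseline score returns 0.99 to 1.01 in every scenario. This is partly by construction, because the score is the only path from diet to outcome in the model.

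The sign is an input. If the exposure is a healthful food, an RR below 1 agrees with the article's hypothesis. If it is processed meat, and symptoms lower intake of it, the same RR runs against the hypothesis.

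**The case against.** The best defence is that the text is more careful than a short quotation suggests. It speaks of giving priority to such studies, of addressing the difficulty, and of directionality or temporality. Diet at baseline, exclusion of prevalent cases and a later outcome do secure temporality relative to detected disorder. Trials are also admitted to strengthen causal conclusions, Textbox 1 is a minimum, and a separate meta-analysis protocol will include meta-regression on methodological biases. All of this is right, and it rules out saying that the article claims to have settled direction.

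It does not remove the point. The article fixes the exclusion, the timing rule and the required models itself, and its Results section has member studies follow the analysis plan presented in the paper. The Abstract describes the 18 recruited studies as longitudinal cohorts, so help from trials is so far only prospective. A later meta-regression cannot use early-case or symptom-adjusted estimates that the cohorts never produced.

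A reader might infer that the bias favours the hypothesis in every cohort. The documents do not support that. They do not say how emerging illness changes any of the 15 GBD exposures, most of which are coded as absolute amounts. Ascertainment also varies: the cutoff mechanism and the baseline score belong to scale-based cohorts, while others use interviews, records or prescriptions.

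A reader might also infer that nothing in the plan separates early from late cases. The subgroup by year does so in part.

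**Conclusion.** The point holds in a limited form. Excluding baseline cases supports a claim of temporality relative to detected disorder. It does not support the phrase that the risks run from diet to disorder and not the reverse. With no minimum interval, subthreshold participants retained in scale-based cohorts and no required adjustment for severity, the stated rules can return a non-null risk ratio when diet has no effect.

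The size is unknown. The illustrations run from 0.97 down to 0.78 per SD for diet-symptom correlations of -0.1 to -0.3. They rest wholly on assumed inputs and attribute the whole diet-symptom association to illness changing diet. They show that the mechanism survives the exclusion; they do not estimate the bias in any cohort or food.

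One might expect a lag analysis alone to restore the directional claim. The simulation argues against that, since a longer interval reduced the false association but left some of it.

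**What to change.** For prospective studies, add to Textbox 1, where data allow:

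- **(a)** Model 2 excluding cases identified in a prespecified initial period (2 years, for example) or at the first follow-up wave.
- **(b)** Model 2 plus the continuous baseline symptom score, where a scale was used.

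Keep both as sensitivity models. Model (a) loses cases and cannot be run in a cohort with a single follow-up. Model (b) may over-adjust if diet contributed to the baseline symptoms.

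In Strengths and Limitations, claim temporality relative to detected disorder, list residual reverse causation as a limitation, and state that direction will be interpreted from (a) and (b) together, not from (a) alone. It would also help to say that the estimates by year will be read for early-case effects.

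The cost is two further runs per exposure-outcome pair on data already held, plus a few sentences. The models need to be specified before the cohort estimates are pooled, so that they are harmonised like the rest.

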### Conclusion

This multicountry, 5-year project has the potential to highlight the role of modifiable lifestyle risk factors in the prevalence and incidence of CMDs. Given the global burden of depression and anxiety, new approaches and targets for their prevention and management are of unprecedented importance.

## Appendix

Multimedia Appendix 1 Commonly used tools and scales for assessing common mental disorders, and their cut-offs for indicative diagnosis.

## Abbreviations

CMD: common mental disorder
GBD: Global Burden of Diseases, Injuries, and Risk Factors Study
GLAD: Global burden of disease Lifestyle And mental Disorders
PRISMA: Preferred Reporting Items for Systematic Reviews and Meta-Analyses
